**Fig. 5 Fig5:**
[figure not shown]
AHA pediatric cardiac arrest algorithm – 2018 update [5]

The scenarios will be conducted in situ in the PED resuscitation bay to increase realism, thus allowing participants to make use of real resources in the actual environment where they are expected to perform CPR. The decision to use or not use any equipment will remain personal, as in real-life situations. All participants in group B will be offered the possibility to hold PALS pocket reference cards in their hands throughout the entire scenarios. Whether they refer to these or not will be left to their entire discretion, similar to real-life settings. The locale will be exclusively devoted to the simulation to prevent unexpected interruptions or external stimuli. Monitoring alarms will be activated to increase realism and stress, and distracting exogenous factors (telephone call, immediate unavailability of specialists, non-essential information, etc.) will occur.

The untimed portion of the simulation will start by turning on the two video cameras (GoPro Hero 7 Black edition; San Matteo, CA, USA) with the team awaiting 10 m away from the resuscitation bay. Participants will then be invited to enter the bay by a study investigator. When entering the bay, a clinical statement to recognize the life-threatening condition of the patient, including his exact weight and age, will be given by the investigator as follows: “Here is Cindy, a 12-kg, 18-month-old girl known for a congenital type 2 long QT syndrome who experienced a witnessed syncope after she suddenly woke up from a nap in her stroller after a loud car horn. She was brought to the emergency department by her parents without prior resuscitation maneuvers and immediately installed in the resuscitation bay as she is unconscious, pale and not breathing”. At this moment, the investigator will ask the team leader to manage the situation with the team, either with the support of InterFACE or conventional methods. According to PALS recommendations, the team will have to start the CPR by assessing the patient with the pediatric assessment triangle [41]. Because of the invariable absence of a pulse in an unconscious and non-breathing child, the team should follow the circulation-airway-breathing approach and start a 2-min cycle of chest compressions and ventilations (15:2 ratio) and use the resuscitation equipment. Goals for this scenario will be to recognize a ventricular fibrillation rhythm and to adhere to the PALS cardiac arrest algorithm. ROSC will ensue after a bolus of 5 mg/kg amiodarone and the subsequent fourth electric shock. After ROSC recognition by the team, the scenario will end and the GoPro cameras turned off.

The team will be asked to exit the bay to have a 10-min rest period in a quiet room, free of cognitive information/tasks. The leader will have to wait separately in another room.

The whole team will then be asked to enter the resuscitation bay for the second scenario adapted from Crozier et al. [42]. When entering the room, the clinical statement will be: “Here is Junior, a 13-kg, 20-month-old boy involved in a high velocity motor vehicle accident 30 min ago. He was brought to the ED with an altered state of consciousness and pallor. A cervical spine collar is in place and the intravenous line was dislodged when he was transferred from the stretcher to the bed”. At this moment, the investigator will ask the team leader and team members to manage the situation similarly to the previous scenario, using InterFACE or conventional methods. They will be expected to progress through the primary and secondary surveys according to ATLS guidelines. Goals for this scenario will be to recognize a hypotensive hypovolemic shock secondary to major blood loss from internal and external injuries and to recognize the signs and symptoms of a closed head injury. The scenario will end and GoPro cameras will be turned off after the patient’s return to a normotensive state following saline boluses and blood transfusions and the decision to perform a computed tomography scan. Moulage (bruises, external blood hemorrhage) will be applied to the manikin in the second scenario to enhance physical findings. Neither pilot testing nor repetitions will be permitted. There will be no educational adjuncts prior to or after the study period. At the study close-out, participants will be instructed not to disclose any information from the scenarios to other participants to prevent any preparation bias.

### Outcome measures

Research using simulation as a valid and reliable investigative methodology to study factors affecting human and systems performance in health care has been reviewed [43]. In this simulation based-study, outcomes will be evaluated by several instruments. Raters will be trained to use the rating instruments in their native language prior to their use. A schematic diagram of the time schedule of data collection for all outcome measures is shown in Table 1. To report the primary and secondary outcomes, we will follow the five levels of specification in reporting outcome measures defined in [44, 45] that include information about the (1) the domain, (2) specific measurement, (3) specific metric to characterize each participant’s results, (4) the method of aggregation, and (5) the time frame that will be used for analysis.

### Primary outcome

#### Situational awareness

Direct measures of SA through the SA global assessment technique (SAGAT) instrument were found to be a highly sensitive, reliable, and predictive measure of individual and team performance in a patient-simulated environment [21]. In this trial, SAGAT questionnaires representing the three SA levels (i.e., perception, comprehension, and projection) were adapted from Coolen et al. [19] by an expert panel of senior pediatric emergency physicians, nurses, and a statistician using a goal-directed task analysis (GDTA) methodology as described by Endsley et al. [46] (Additional file 2). SA (domain) expressed as a score in absolute value in conjunction with percentage (metric) will be measured using the SAGAT (specific measurement) during video review of each scenario. Both the individual participant SAGAT score and the team SAGAT score, defined as the degree to which each team member possesses the SA required for their role and calculated as the sum of individual SAGAT scores, will be calculated [42, 47]. The SAGAT scores will be further divided into their three dimensions to individually evaluate perception, comprehension, and projection of each team member and to compare them to what truly happened during the simulation. This will be done similarly for the TSAGAT. According to Endlsey et al. [46], the SAGAT responses for categorical variables will be scored as either correct (1) or incorrect (0) by two of the investigators. For numerical responses, answers will be considered correct based upon a 10% pre-defined tolerance range settled by the research investigators around the true value. Higher SA scores will denote higher SA. Mean overall scores will be aggregated to compare both study arms (method of aggregation). The time frame of interest for this endpoint is over the duration of the whole CPR scenario.

Practically, each scenario will be frozen three times (2-min duration per freeze; queries’ length will be compatible with time constraints) at random points in time during the scenario to issue queries chosen randomly from a predefined list (Additional file 3). Random freezes have been shown not to impact on participant performance measures [46] and to limit recall bias that could otherwise arise if queries are asked at the end of the simulation [21]. This will allow to assess respondents’ awareness of the current situation so that query occurrence will not be associated with the occurrence of specific related events [46]. During each freeze, participants will be asked to complete a total of eight multiple choice queries for level 1, four for level 2, and four for level 3 of SA in a written confidential manner. We will therefore collect per scenario a total of 768 SAGAT queries and eight TSAGAT, with a range of possible scores of 0 to 16 on each SAGAT questionnaire and a combined total score of 0 to 96 on TSAGAT. Over the course of the experiment, this will represent a total of 96 SAGAT (768 queries) and 16 TSAGAT. No freezes will occur earlier than 5 min after the beginning of the scenario to allow participants to build up a representation of the situation [46]. The second and third freezes will be interspaced at least 1 min from each other and from the first freeze.

### Secondary outcomes

#### Leadership

Leadership (domain) will be measured with the resuscitation team leader evaluation (RTLE) instrument (specific measurement) [48]. This instrument developed by Grant et al. encompasses four leadership concepts: (1) the physical and verbal leader’s position, (2) communication and delegating skills, (3) ability to assess, adapt and anticipate, and (4) ability to ask for internal and external help [48]. It comprises 12 items rated on a 4-point Likert scale (metric) from 0 (not performed) to 3 (performed well, consistently) to score leadership and communication skills (Additional file 4). A not applicable (N/A) category is also available for those items not relevant to the scenario. For the purpose of this trial, we will remove items 1 and 12 as the leader will be clearly identified from the beginning of the scenario and teams will not be advised to ask for external help. Therefore, the total item score expressed as an absolute value will range from 0 to 30. Mean overall scores will be aggregated to compare both study arms (method of aggregation). The time frame of interest for this endpoint is over the duration of the whole CPR scenario.

#### Team performance

Leadership, communication skills, team work, task management, and the team’s overall performance (domains) will be measured as scores obtained from the team emergency assessment measure (TEAM) instrument (specific measurement) [49]. Although a number of tools are available for assessing teamwork performance, the TEAM stands out as the most valid and reliable instrument to use in emergency departments [50]. TEAM comprises 11 items rated on a 5-point Likert scale from 0 (never/hardly) to 4 (always/nearly always), which are summed up into a total item score (metric) expressed as an absolute value ranging from 0 to 44 [49]. The final score obtained allows to assess the performance of the emergency medical team based on three categories: leadership (items 1 and 2); teamwork (items 3 to 9); and task management (items 10 and 11). Items 8 and 9 relate to SA perception and projection, respectively. Furthermore, the team’s overall performance is rated through a twelfth item on a global rating scale of 1 to 10 (higher score denotes better performance) (Additional file 5). Mean overall scores will be aggregated to compare both study arms (method of aggregation). The time frame of interest for this endpoint is over the duration of the whole CPR scenario.

#### Time to critical life-saving maneuvers

Team effectiveness (domain) will also be measured on video reviewing (specific measurement) as the time spent in seconds by the team to achieve the pre-designed goals set out by the AHA for the PALS course and the American College of Surgeons for the ATLS course [10, 51, 52]. They will comprise the elapsed time in seconds between the end of the clinical statement by the study investigator to (1) ventricular tachycardia or hypotensive shock recognition; (2) initiation of chest compression; (3) time to each defibrillation attempt; (4) time to administration of intravenous drugs, volume expansion with 0.9% sodium chloride or blood transfusion; and (5) time interval between defibrillation attempts (metrics). If not achieved within the 40-min scenario, this will be considered as a lack of goal completion. It should be noted that for the trauma scenario, we decided not to use the modified non-technical skills scale for trauma (T-NOTECHS). This decision is based on the serious risk of assessment bias with this instrument, as emphasized by the consensus-based standards for the selection of health measurement instruments (COSMIN) [50]. Mean times per goals will be aggregated to compare both study arms (method of aggregation). The time frame of interest for this endpoint is over the duration of the whole CPR scenario.

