**Methods:**

We will conduct a prospective, cluster randomized controlled trial by groups of 6 participants in a tertiary pediatric emergency department (33,000 consultations/year) with pediatric physicians and nurses. We will compare the impact of the InterFACE tool with conventional communication methods on SA and effective team communication during a standardized pediatric in-hospital cardiac arrest and a polytrauma high-fidelity simulations. Forty-eight participants will be randomized (1:1) to consecutively perform two 20-min video-recorded scenarios using either the mHealth tool or conventional methods. The primary endpoint is the SA score, measured with the Situation Awareness Global Assessment Technique (SAGAT) instrument. Enrollment will start in late 2020 and data analysis in early 2021. We anticipate that the intervention will be completed by early 2021 and study results will be submitted in mid 2021 for publication.

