On the day of participation, each subject will complete an anonymous survey about basic demographic information, professional length of medical training, PALS and ATLS training, and simulation and computer experience. After random allocation, each team will receive: (1) a standardized 15-min training session on how to use the app, (2) a presentation of the simulation manikin’s characteristics, and (3) the topics of three assessment questionnaires (see below), but to prevent unblinding, not the queries themselves. The teams will then be asked to consecutively perform two 20-min highly realistic, scripted CPR scenarios on a high-fidelity WiFi manikin (Laerdal SimBaby, Laerdal Medical, Stavanger, Norway). High levels of realism are known to immerse participants in the simulated experience and prevent confounding variables that might potentially affect the way they perform [30]. Within each scenario, three separate “freeze” periods will occur at random points in time to assess the shared and complementary SA of each team member individually regarding the CPR in progress. During freezes, the entire team will have to turn away from the patient, monitors and app to “blank out” the simulator and avoid any cognitive help from the simulated environment that could otherwise bias the respondent’s answers to the questionnaires. The scenarios will be standardized to strictly follow the 2018 AHA pediatric ventricular fibrillation algorithms [5] (Fig. 5) and the 2018 ATLS guidelines [40]. They will be extensively tested before the trial to achieve optimum functioning on the day of participation and performed on the same high-fidelity manikin already primed with vital signs appropriate for the scenarios. Both scenarios will be completed in the same order and the procedure will be standardized across all teams to follow the same chronological progression and range of difficulty in order to ensure that each participant is exposed to exactly the same case, with similar challenges in technical and non-technical skills. The uniform delivery of the scenarios throughout the entire study will minimize confounders. Study investigators will allow progression through the scenarios only once predefined milestones have been reached, irrespective of error occurrence or the time taken to achieve them.

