Kaplan–Meier curves for the time elapsed between the end of the clinical statement by the study investigator and timed secondary outcomes will be compared using the log-rank (Mantel-Cox) test including a cluster term to account for the cluster randomized design. Wrong defibrillation or drug doses will be measured as a deviation from the amount of energy delivered in Joules or drug doses in milliliters compared to 2018 AHA PALS cardiac arrest algorithm, respectively. Use of epinephrine 0.1 mL/kg (0.1 mg/ml concentration) and amiodarone 5 mg/kg (150 mg/3 mL concentration) are expected for the first scenario. We define an emergency medication dose administration error as a deviation from the correct weight dose of more than 10% [55]. Moreover, defibrillations (in Joules) and the number of shocks will be also measured during the first scenario. Defibrillation doses of 2 J per kg for the first attempt and 4 J per kg for the subsequent second, third and fourth attempts are expected [5]. A GEE model with a Poisson link will be used to assess the relationship between absolute errors in defibrillation and drug doses expressed as categorical variables. Wrong defibrillation mode will be also measured. Absolute deviations will be analyzed. The mean (SD) difference obtained with each intervention method will be reported with a 95% CI. Univariable linear GEE with 95% CI will be performed to assess whether time to initiation of chest compression, defibrillation attempts, and drug delivery are associated with prior resuscitation experience as a clinician in real-life and simulated environments. Similar analyses will be carried out for errors in fluid resuscitation volumes (in milliliters) and blood transfusion during the second scenario. An initial 20 mL/kg bolus of isotonic crystalloid followed by 10–20 mL/kg of packed red blood cells and 10–20 mL/kg of fresh frozen plasma and platelets are expected [40].

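### The time-to-goal outcome uses a 40-min non-completion limit that fits no scenario, names a rhythm that scenario 1 does not script, and compares mean times that have no value for a goal not reached

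*Protocol article*

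**What the plan says.** The protocol article, under Time to critical life-saving maneuvers, measures seconds from the end of the investigator's clinical statement to a list of goals. The first is "ventricular tachycardia or hypotensive shock recognition". The rule for a goal not reached is "If not achieved within the 40-min scenario, this will be considered as a lack of goal completion". The arm comparison is "Mean times per goals will be aggregated to compare both study arms".

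Other sections bear on each of these three elements:

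- **Duration.** Under Intervention and resuscitation scenarios, teams will "consecutively perform two 20-min highly realistic, scripted CPR scenarios on a high-fidelity WiFi manikin". The Abstract has them randomized "to consecutively perform two 20-min video-recorded scenarios", and Table 1 shows two scenarios of 20 min. Each scenario opens with its own clinical statement. After the first, the cameras go off and the team rests for 10 min.
- **Rhythm.** The intervention section says of scenario 1: "Goals for this scenario will be to recognize a ventricular fibrillation rhythm". It also ties that scenario to the pediatric ventricular fibrillation algorithm.
- **Analysis.** Under Statistical analyses, Kaplan-Meier curves for the timed outcomes "will be compared using the log-rank (Mantel-Cox) test including a cluster term". That section also plans univariable linear GEE relating some of these times to prior experience, and complete-case analysis if data are missing.

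**The concern.** A time-to-event outcome needs an origin, an event and a point at which observation stops. The origin is clear here. The stopping point is given as the length of a scenario that does not exist, and one event is named differently from the script. Two video raters working independently need one definition of each.

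The choice of summary matters because there are so few teams. The paragraph foresees goals that are not reached, yet compares arms by mean times and assigns those goals no time. If they are handled as missing data, the complete-case rule removes them, and the team removed is the one that did worst on that goal. The planned linear GEE on times has the same gap. The Kaplan-Meier and log-rank analysis does not, because it can keep such teams as censored. The protocol thus names two summaries for one outcome, and they treat the slowest teams differently.

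**Working it through.** **1. Where 40 comes from.** Inputs: two scenarios of 20 min (Abstract, Table 1, intervention section) and a 10-min rest between them (intervention section).

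- One scenario: 20 min = 1,200 s.
- Both scenarios added: 2 × 20 = 40 min = 2,400 s. This is the only combination that gives the stated figure.
- With the rest: 40 + 10 = 50 min.

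The sum cannot serve as the limit for a single goal. Every time restarts at its own scenario's clinical statement. Goals such as defibrillation belong to the arrest case, and shock recognition and transfusion belong to the trauma case. Recording stops between the two.

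**2. What a per-scenario limit could be.** The primary outcome section gives three freezes of 2 min per scenario: 3 × 2 = 6 min. Data collection and management deducts freeze time from the scenario duration.

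- Freezes outside the 20 min: net limit 20 min = 1,200 s.
- Freezes inside the 20 min: 20 − 6 = 14 min = 840 s.

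The text does not say which applies. The 60-min observation period per team does not settle it, since 20 + 10 + 20 = 50 min, or 50 + 2 × 6 = 62 min with freezes added.

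**3. The rhythm.** The outcome section times recognition of ventricular tachycardia. The intervention section scripts ventricular fibrillation. Pulseless ventricular tachycardia otherwise appears only in the name of the joint algorithm shown in the app (Fig. 3 legend) and in the abbreviation list.

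**4. Weight of one non-completing team.** Power and sample size calculation gives 8 teams. At 1:1 that is 8 / 2 = 4 per arm, so one team is 1/4 = 25% of an arm.

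The mean depends on a rule that the protocol does not give. Let three teams complete at *c* seconds (an assumption, shown over a range) and one not complete. The arm mean is *c* if that team is dropped, and (3*c* + *L*) / 4 if it is assigned a limit *L*:

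| *c* (s) | dropped | *L* = 840 s | *L* = 1,200 s | *L* = 2,400 s |
|---|---|---|---|---|
| 120 | 120 | 300 | 390 | 690 |
| 300 | 300 | 435 | 525 | 825 |
| 600 | 600 | 660 | 750 | 1,050 |

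For *c* = 300 and *L* = 1,200: (900 + 1,200) / 4 = 525. These rows show sensitivity to a missing rule. They do not predict the trial's results.

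**5. The log-rank test.** Its statistic sums, over event times, observed minus expected events, with expected = events × (arm at risk / total at risk). If scenarios stop at 20 min, every event falls at or before 1,200 s. A team censored at 1,200 s or at 2,400 s is then at risk at every event time, so the statistic is the same. If a scenario runs over, the limit matters: a goal reached at 22 min is an event under a 40-min rule and a non-completion under a 20-min rule.

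**The case against.** The strongest reply is that these are slips of wording with little consequence. Several parts of it stand.

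- **No time is assigned to non-completers.** The protocol records a lack of completion, which is a status. A reader might infer that such teams are coded at 2,400 s, which would move a four-team mean by (2,400 − 1,200) / 4 = 300 s compared with coding at 1,200 s. The text contains no such rule.
- **The named test copes.** The log-rank test keeps non-completers as censored and is unchanged under a 20-min stop. It would be wrong to say that the 40-min figure invalidates it.
- **Non-completion may be rare.** Investigators let a scenario advance only at predefined milestones, however long these take, and may step in on a significant deviation from the algorithm. This also means that 20 min is not clearly a hard stop, so simply writing 20 in place of 40 would choose one reading without reconciling the sections.
- **The rhythm is probably inferable.** Read literally, all 8 teams would fail the recognition goal. Raters who know the script would most likely score the scripted rhythm, so the documents do not support that outcome as a realistic one.
- **A mean can include non-completers.** A restricted mean does so. The difficulty is only that the plain mean comes without a rule.

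It can also be said that the mean-time sentence fills a slot in a reporting template repeated for other outcomes, and that handling of non-completers belongs in a SAP. That would excuse silence. It does not excuse a stated limit and a stated event that disagree with the scenarios, or two sections that name different summaries.

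**Conclusion.** The point holds as a correction to the definition of one secondary outcome. The 40-min limit matches no scenario. The first timed event disagrees with the scripted rhythm. The mean-time comparison is not aligned with the Kaplan-Meier and log-rank plan.

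The practical size is that one non-completing team is 25% of an arm. A complete-case mean would lose that quarter, and it is the slowest team. This assumes four teams per arm, at least one goal not reached, and non-completion handled as missing, which the protocol neither states nor excludes. How often goals will be missed cannot be judged from the document.

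The primary endpoint and the sample size are untouched. The planned log-rank comparison is affected only if scenarios may run beyond 20 min.

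**What to change.** 1. Replace the 40-min figure with a per-scenario limit consistent with the 20-min scenarios. Reconcile it with the milestone-driven progression by saying whether a scenario can overrun, and state whether the deducted freezes fall inside the limit. Censor teams that do not reach a goal at that limit, or at the actual end of the scenario.
2. Reconcile the rhythm named in the outcome section with the one scripted in the intervention section, so that raters score a single defined event.
3. Replace the plain mean-time comparison with a summary that keeps non-completers, such as the Kaplan-Meier median or the restricted mean up to the scenario limit, in line with Statistical analyses. State how the linear GEE on times treats goals not reached.

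The cost is protocol wording only, with no extra data and no change to the number of teams. It is best done before video rating begins.
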